## Abstract

**Background:**

Chronic knee pain is a common and disabling condition in people over 50 years of age, with knee joint osteoarthritis being a major cause. Acupuncture is a popular form of complementary and alternative medicine for treating pain and dysfunction associated with musculoskeletal conditions. This pragmatic Zelen-design randomised controlled trial is investigating the efficacy and cost-effectiveness of needle and laser acupuncture, administered by medical practitioners, in people with chronic knee pain.

**Methods/Design:**

Two hundred and eighty two people aged over 50 years with chronic knee pain have been recruited from metropolitan Melbourne and regional Victoria, Australia. Participants originally consented to participate in a longitudinal natural history study but were then covertly randomised into one of four treatment groups. One group continued as originally consented (ie natural history group) and received no acupuncture treatment. The other three were treatment groups: i) laser acupuncture, ii) sham laser or, iii) needle acupuncture. Acupuncture treatments used a combined Western and Traditional Chinese Medicine style, were delivered by general practitioners and comprised 8–12 visits over 12 weeks. Follow-up is currently ongoing. The primary outcomes are pain measured by an 11-point numeric rating scale (NRS) and self-reported physical function measured by the Western Ontario and McMaster (WOMAC) Universities Osteoarthritis Index subscale at the completion of treatment at 12 weeks. Secondary outcomes include quality of life, global rating of change scores and additional measures of pain (other NRS and WOMAC subscale) and physical function (NRS). Additional parameters include a range of psychosocial measures in order to evaluate potential relationships with acupuncture treatment outcomes. Relative cost-effectiveness will be determined from health service usage and outcome data. Follow-up assessments will also occur at 12 months.

**Discussion:**

The findings from this study will help determine whether laser and/or needle acupuncture is efficacious, and cost-effective, in the management of chronic knee pain in older people.

**Trial registration:**

Australian New Zealand Clinical Trials Registry reference: ACTRN12609001001280

## Background

Chronic knee pain is a common and disabling condition, particularly in people over 50 years of age
[1,2]. Knee joint osteoarthritis (OA) is a major cause of knee pain and results in loss of functional independence, psychological impairment and a reduction in the overall quality-of-life of affected individuals. In addition to the personal burden of knee OA, there are substantial direct and indirect health care costs particularly in terms of employment status, productivity and joint replacement surgery, making knee OA a substantial public health problem.

Management of knee OA is primarily focused on treating the pain and disability associated with the condition, with non-pharmacological therapies considered the cornerstone of treatment
[3]. Acupuncture is a popular treatment for pain and dysfunction associated with musculoskeletal conditions. A study of 350 rheumatology patients in the United Kingdom revealed that 61% of those with OA had used acupuncture
[4]. In clinical practice, a range of health professionals administer or refer patients for acupuncture. In Australia, acupuncture by medical practitioners has been established for 40 years and has gained widespread patient acceptance in the community. We have found that over 80% of surveyed general medical practitioners referred patients for acupuncture
[5] and that they generally consider acupuncture to be highly effective and safe
[6]. Amongst all complementary and alternative medicine modalities, acupuncture is associated with the highest average annualised expenditure
[7]. Thus research to determine its efficacy and cost-effectiveness is warranted.

Acupuncture traditionally involves the insertion of fine needles into specific points of the body. According to the ancient philosophy of traditional Chinese acupuncture, energy circulates in 12’meridians’ located throughout the body. Pain or ill health will result if the meridian energy circulation is blocked. Stimulating the appropriate combination of meridian acupuncture points in the body can restore energy circulation, health, and balance
[8]. From a Western medicine perspective, acupuncture is a technique of peripheral sensory stimulation (through activation of peripheral A-delta and C fibres) applied at acupuncture points and/or trigger points that can activate central nervous system pain pathways, release specific pain relieving substances as well as reduce muscle and sympathetic nervous system tonicity
[9,10].

In recent years there has been a substantial increase in the number of randomised controlled trials (RCTs) investigating the efficacy of needle acupuncture for chronic knee pain. A recent meta-analysis concluded that while placebo-controlled trials show statistically significant benefits for pain, the benefits are small and unlikely to be clinically relevant
[8]. Waiting list-controlled trials however suggest statistically significant and clinically relevant benefits, which may be due to expectation or placebo effects. Accordingly, well-designed rigorous RCTs are needed that control for both placebo and expectation effects in order to evaluate the efficacy of acupuncture for chronic knee pain.

Although acupuncture has been traditionally administered with needles, the use of laser acupuncture has increased because of its pain-free nature and minimal adverse effects
[11]. Laser acupuncture involves the application of low-level laser, which is a form of electromagnetic radiation in the visible or infrared region of the light spectrum. These laser devices are manufactured with such low energy densities that photo-chemical changes are elicited without photo-thermal effects. Within these ranges, various energy levels and wavelengths can be used depending on the tissue penetration required. In laser acupuncture, the beam of light generated is applied to the skin at acupuncture points and/or trigger points, similar to the application of needles.

Laser acupuncture effects are thought to alter peripheral afferent nerve stimulation, modulating spinal cord afferent input on second order neurons and enhancing peripheral endogenous opioid analgesia
[12] as well as acting via centrally mediated mechanisms. Laser also has effects at the local cellular and tissue level
[13] with evidence of modulation of inflammatory processes
[14] varying according to laser dosage
[15].

In contrast to needle acupuncture, the efficacy of laser acupuncture has been less well studied in the management of chronic knee pain. In general, RCTs have used small sample sizes and variable laser dosages in terms of wavelength, total energy, application sites and number of treatments. In a meta-analysis of eight trials published up until 2006 investigating the short-term efficacy (within 4 weeks) of laser therapy for knee OA, statistically and potentially clinically significant pain-relieving benefits over placebo were found
[11]. The effect was greater when only trials evaluating an optimal dosage and administration were included. Since this meta-analysis, two other small studies have been published providing further support for the use of laser acupuncture in chronic knee pain
[16,17].

It is not clear whether differences in efficacy exist between laser and needle acupuncture given that there are no direct head-to-head comparisons of needle and laser acupuncture for chronic knee pain., However, in a systematic review, laser but not needle acupuncture offered statistically and clinically significant short-term pain relief over placebo
[11]. Similarly, a meta-analysis found that treatment with laser acupuncture had better pain outcomes in the medium-term, although not short-term, than treatment with needle acupuncture in people with non-specific neck pain
[18]. These studies suggest that laser acupuncture may be at least as effective, if not more effective, than needle acupuncture.

It is apparent that there is a need for further evaluation of acupuncture in the management of chronic knee pain. This is highlighted by discrepancies in recommendations by clinical guidelines – the Osteoarthritis Research Society International currently recommend acupuncture
[3], the United Kingdom NICE clinical guidelines could not give a firm recommendation due to insufficient evidence
[19] and the American College of Rheumatology
[20] conditionally recommend acupuncture but only for patients with moderate to severe pain who are candidates for joint replacement but are unwilling/unable to have surgery. Furthermore, there is limited information about the maintenance of acupuncture effects with no studies reporting a follow-up longer than three months.

In designing appropriate clinical trials, a methodological concern in acupuncture trials has been the difficulty in having a true placebo control group given pre-existing participant expectations, particularly where the treatment itself is multidimensional involving therapist-patient interaction as well as an intervention
[21]. A meta-analysis has confirmed a significant placebo effect for the treatment of pain in knee OA that varies in size depending on the intervention
[22]. For acupuncture, the placebo effect size (mean 0.71 (95% confidence interval 0.53, 0.90)) was higher than the overall effect size for all placebo treatments (0.51 (0.46, 0.55)). As with many treatments, higher patient expectation has been shown to be associated with greater improvements following acupuncture treatment. A pooled analysis of four clinical trials of acupuncture found that after completion of treatment, the odds ratio for response between patients considering acupuncture an effective or highly effective therapy and patients who were more sceptical was 1.67 (95% confidence interval 1.20-2.32)
[23]. The use of “sham needle” acupuncture as a placebo control, whereby needling is performed superficially or at non-acupuncture sites, is controversial given that such a procedure may still produce biological responses and hence may not be truly placebo. Blinding of clinicians administering needle acupuncture is also problematic. Such methodological difficulties can be overcome in trials of laser acupuncture as it is possible to successfully blind both participants and clinicians by using specially designed laser machines
[24].

First described by Zelen in the New England Journal of Medicine in 1979
[25], Zelen design trials are a means of reducing bias by minimizing participant expectations in a treatment trial where the knowledge of the intervention itself may influence the study outcome (Hawthorne effect) in the control group. This is done by enrolling participants into an observational study but covertly randomising participants following their recruitment into a treatment trial (post-randomised consent). The control group remains unaware of the treatment being evaluated
[26]. Such a design has been used successfully in a study comparing a physiotherapy treatment of exercise and knee taping to standard non-physiotherapy treatment in people with predominant patellofemoral OA
[27]. A potential disadvantage of the Zelen design can be a higher crossover rate than a usual RCT which may dilute treatment effects in an intention-to-treat analysis. However, a review of 58 RCTs using the Zelen design found that while most trials (n = 41) experienced some crossover from one group to the other (median crossover = 8.9%, interquartile range 2.6% to 15%) the rate was usually within acceptable limits
[26].

Thus, we are currently conducting a Zelen design RCT to investigate the efficacy of needle and laser acupuncture administered by experienced medical acupuncturists in people with chronic knee pain and to evaluate maintenance of effects over the longer term. We will also evaluate the cost-effectiveness of needle and laser acupuncture, as well as explore whether psychosocial measures are associated with changes in pain, physical function and health-related quality of life following acupuncture treatment. This paper describes the protocol for this ongoing trial.

The primary hypotheses are that:

H1: Laser acupuncture will result in significantly greater improvements in pain (as measured overall via numerical rating scale (NRS)) and physical function (as measured via Western Ontario and McMaster (WOMAC) Universities Osteoarthritis Index) than sham laser acupuncture at 12 weeks.

H2: Laser and needle acupuncture will result in significantly greater improvements in pain (as measured overall via NRS and physical function (as measured via WOMAC) than no treatment at 12 weeks.

H3: Laser acupuncture will result in significantly greater improvements in pain (as measured overall via NRS) and physical function (as measured via WOMAC) than needle acupuncture at 12 weeks.

The secondary hypotheses are that:

H4: Sham laser acupuncture will result in significantly greater improvements in pain (as measured overall via NRS) and physical function (as measured via WOMAC) than no treatment at 12 weeks.

H5: Laser, sham laser and needle acupuncture will result in significantly greater improvements in pain (as measured overall via NRS) and physical function (as measured via WOMAC) than no treatment at 12 months, while laser acupuncture will result in significantly greater improvements than needle acupuncture.

H6: Laser, sham laser and needle acupuncture will result in significantly greater improvements in pain (as measured on standing and walking via NRS and by WOMAC), physical function (as measured via NRS) and health-related quality of life than no treatment at 12 weeks and 12 months.

H7: Laser acupuncture will result in significantly greater improvements in pain (as measured on standing and walking via NRS and by WOMAC), physical function (as measured via NRS) and health-related quality of life than needle acupuncture at 12 weeks and 12 months.

H8: A greater proportion of people receiving laser, sham laser and needle acupuncture will report global overall improvements compared to no treatment at 12 weeks and 12 months.

H9: A greater proportion of people receiving laser acupuncture will report global overall improvements compared to needle acupuncture at 12 weeks and 12 months.

## Methods/Design

### Trial design

A two-stage Zelen design RCT
[25,28] which conforms to CONSORT
[29] and STRICTA guidelines
[30] for acupuncture studies (Figure 
1). 

**Figure 1 F1:**
[figure not shown]
Flow diagram of study protocol.

### Participants

A total of 282 men and women with chronic knee pain have been recruited from the community in metropolitan Melbourne and regional Victoria, Australia. A number of recruitment strategies were used including (i) advertisements in local clubs, community centres, newspapers, Arthritis Australia and University websites, University staff newsletters, radio, television, and a social networking site; (ii) placement of brochures and study posters in medical and physiotherapy clinics; and (iii) presentations about knee OA in the local community by the researchers.

People were eligible to participate if they (i) were aged >50 years; (ii) had a history of knee pain of >3 months duration; (iii) reported knee pain on most days of the past month; (iv) reported an average knee pain severity over the past month of ≥ 4 out of 10 on an 11-point NRS and; (v) reported morning knee stiffness of <30 minutes duration.

Exclusion criteria included: (i) history of any systemic arthritic condition; (ii) history of knee arthroplasty on the most painful knee; (iii) wait-listed for any knee surgery for either knee; (iv) history of any knee surgery in previous 6 months; (v) any other condition affecting lower limb function (eg trauma, malignancy, neurological condition); (vi) history of any knee injection in past 6 months (eg cortisone, hyaluronic acid); (vii) current use of oral or injectable anticoagulant medication; (viii) use of acupuncture in past 12 months; (ix) any bleeding disorder; (x) allergy to light; (xi) referral to pain clinic or use of morphine or pethadine within past 6 months; (xii) any other medical condition precluding participation in the trial (eg kidney or liver disease, deep vein thrombosis); (xiii) knee pain subject to compensation claim or; (xiv) unable to give written informed consent.

Although both knees could undergo treatment as part of the project, only the most symptomatic knee as nominated by the participant at enrolment was evaluated.

### Procedure

Figure 
1 depicts the trial protocol. Eligibility of prospective participants was determined over the telephone by an investigator (MK) not involved in assessment or treatment of participants. Ethical approval was obtained from the University of Melbourne Human Research Ethics Committee (HREC No. 0931840). All participants provided written informed consent. Initially, all participants consented to participate in a longitudinal observational natural history study of chronic knee pain, involving assessments at baseline, 12 weeks and 12 months. All assessments, comprised solely of questionnaires, are completed by participants at home and mailed back to the University of Melbourne, where data is entered by a blinded assessor (MK).

Upon receipt of completed baseline questionnaires, an investigator (KN) accessed the computerised covert randomisation schedule to reveal whether the participant was allocated either (i) laser acupuncture (could be either real laser or sham laser but the investigator and participant are blinded to this information); (ii) needle acupuncture or; (iii) no treatment (control group). Participants randomised into the no treatment arm continue as consented in the natural history observational cohort for the 12 month duration of the study and did not undergo (or are made aware of) any intervention as part of the trial. Participants randomised to receive either laser or needle acupuncture were telephoned by an investigator (KN) and offered the opportunity to undergo the allocated intervention and contribute their data to the trial. Participants allocated to the laser groups were informed they may receive either real laser or sham laser and that this has been randomly pre-determined and would not be revealed to them until the completion of the 12 month assessments. Participants willing to participate in the intervention provided informed consent to do so at this point. Participants who choose not to participate in the intervention continued as initially consented in the natural history observational cohort for 12 months, however their data will be analysed as per intention-to-treat.

Participants who were randomised to receive acupuncture had treatment visits arranged with a project general practitioner (GP) for treatment over 12 weeks. All study participants, including those allocated to the no treatment group and those who were randomised to receive treatment but declined to do so, undergo re-assessment at 12 weeks and again at 12 months.

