### Sample size calculations

Our primary endpoints are average overall knee pain measured on a NRS and physical function measured via WOMAC at 12 weeks. The minimum clinically important difference to be detected in OA trials is a change in pain of 1.8 units (on NRS)
[47] and a change of 6 physical function units on the WOMAC (out of 68)
[48]. Calculations are based on an analysis of covariance (ANCOVA) adjusting for baseline of the outcome variable, and assume a between-patient standard deviation of 3.0 units for pain and 12.0 units for WOMAC
[49]. Sample size calculations for our particular study design need to take into account four aspects: clustering effects resulting from treatment of patients by the same therapist for comparisons with the control arm (hypothesis H2); dilution of the treatment effect resulting from the Zelen design
[50]; precision gain from baseline adjustment; and loss to followup. Initially assuming no clustering effects and a regular two-arm parallel RCT design with complete followup, 33 patients per arm would be required to detect the above differences in pain and function with 80% power at a two-sided 5% significance level, using ANCOVA with assumed baseline to 12 week correlations of 0.50 for pain and 0.70 for function
[49]. Adopting a conservative intra-therapist correlation of 0.10 inflates the sample size to 40 patients per arm across a total of 10 therapists. Assuming a conservative 15% non-consent rate for patients randomised to any of the three treatment arms increases the sample size by 1/(1–0.15)^2^ = 38%, and finally, allowing for 15% loss to followup, inflates the total sample size to 66 patients per arm, which we round up to 70 per arm, or 280 patients in total. Assessment of hypotheses H1 and H3 involve within-therapist comparisons only and therefore the precision loss from clustering by therapist does not apply, yielding greater power (90%) for these comparisons.

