### Statistical analyses

The primary analysis of the data will be undertaken using the principle of intention-to-treat with all randomised patients included in the analyses. Demographic and clinical characteristics, as well as baseline data, will be presented to assess the baseline comparability of the intervention groups. Descriptive statistics will be presented for each group as the mean change (standard deviation, 95% confidence intervals) in the outcomes from baseline to each time point. Differences in mean change from baseline to each time point will be compared between groups using random effects linear regression modelling adjusting for baseline levels of the outcome measure and using the treating therapists as random effects to account for clustering of outcomes by therapists. Model assumptions will be checked by standard diagnostic plots. Improvement between acupuncture groups (based on the perceived ratings of change) will be compared using logistic regression with random effects as above and presented as odds ratios with 95% confidence intervals. Multiple imputation methodology will be employed to account for missing data
[51]. No statistical adjustment will be made for multiple testing. All tests will be two sided and carried out at the 5% level of significance.

As part of the secondary analyses of the primary outcomes at 12 weeks and 12 months, we plan to conduct a separate analysis to estimate the effect of treatment in the hypothetical scenario of full adherence to the randomised treatment intervention. Analytical methods for this will utilise instrumental variables methodology involving two stage least squares estimation
[52].

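### For laser versus sham, a direct comparison of participants who accepted the offer would estimate the effect under treatment more precisely than the planned two-stage least squares

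*Protocol article*

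**What the plan says.** The Procedure section sets out how laser participants are invited. The investigator who opens the allocation and makes the call learns only that the arm is laser, which "could be either real laser or sham laser but the investigator and participant are blinded to this information". The offer is worded identically for both arms: "Participants allocated to the laser groups were informed they may receive either real laser or sham laser". The decision is taken during that contact: "Participants willing to participate in the intervention provided informed consent to do so at this point". Treatment visits are arranged afterwards. Under Randomisation and allocation concealment, the list is held by someone outside recruitment, assessment and treatment. Under Blinding, the treating GPs are also unaware of real versus sham.

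Those who decline receive neither real nor sham laser. They "continued as initially consented in the natural history observational cohort for 12 months, however their data will be analysed as per intention-to-treat". The Statistical analyses section then applies the "principle of intention-to-treat with all randomised patients included in the analyses" to every hypothesis. Under Sample size calculations the resulting dilution is allowed for: "Assuming a conservative 15% non-consent rate for patients randomised to any of the three treatment arms", the protocol inflates the sample accordingly. For the effect under full adherence, the Statistical analyses section plans a secondary analysis of the primary outcomes by two-stage least squares, for all contrasts alike.

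**The concern.** One approach to decliners is used for contrasts that differ in kind. Against no treatment, the control arm receives no offer at all. Against needle, the offer is a different one. In both cases acceptors may differ between arms, so a comparison of acceptors would be open to selection, and an instrumental-variable method is a sensible way to reach the effect under treatment.

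Laser versus sham is different. The offer is the same, the caller and the participant are both blind, and the decision precedes treatment, so acceptance cannot depend on which laser was allocated. Comparing acceptors directly is then as free of selection as comparing everyone randomised. Two-stage least squares reaches the same quantity indirectly: it takes the diluted all-randomised difference and divides it by the acceptance proportion, which carries the decliners' noise into the estimate. What is at stake is precision in the secondary estimate for the trial's only placebo-controlled contrast.

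**Working it through.** **Inputs (Sample size calculations).** Differences 1.8 (pain) and 6 (function); SD 3.0 and 12.0; baseline correlation 0.50 and 0.70; two-sided 5%; 15% non-consent; 15% loss; 70 per arm.

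**The plan's own figures.**
- Residual SD = SD × √(1 − r²): 3.0 × √0.75 = 2.598; 12.0 × √0.51 = 8.570.
- Per arm for 80% power: 32.7 (pain) and 32.0 (function), so 33.
- Clustering: 32.7 × (1 + (3.3 − 1) × 0.10) = 40.2, so 40.
- Non-consent: 40/0.85² = 55.4, so 56. Loss: 56/0.85 = 65.9, so 66, which the protocol rounds up to 70.
- H1 power with decliners kept and no clustering: 70 × 0.85 = 59.5 per arm. SE = residual SD × √(2/59.5) = 0.476 and 1.571. Diluted differences are 1.8 × 0.85 = 1.53 and 6 × 0.85 = 5.1. Power = 89.5% and 90.1%.

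The stated 90% is reproduced, so it already includes the decliners.

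**Two routes to the effect in those who took up treatment, at 15% non-consent.**

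| | Pain | Function |
|---|---|---|
| Two-stage least squares SE (all-randomised SE/0.85) | 0.476/0.85 = 0.560 | 1.571/0.85 = 1.848 |
| Acceptors directly, 59.5 × 0.85 = 50.6 per arm | 0.517 | 1.704 |
| Ratio of SEs | 1.08 | 1.08 |
| 95% half-width (1.96 × SE), two-stage least squares | 1.10 | 3.62 |
| 95% half-width, acceptors | 1.01 | 3.34 |
| Power | 89.5% vs 93.6% for acceptors | 90.1% vs 94.1% for acceptors |

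The ratio is 1/√(1 − non-consent), whatever the outcome: 1/√0.85 = 1.08. At the 8.9% median crossover cited in the Background it is 1/√0.911 = 1.05, and pain power is 93.1% against 95.0%.

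**Validity, by simulation of the pain outcome** (70 per arm, 15% loss, acceptance dependent on baseline and prognosis, and an assumed common response of 1.5 units in anyone treated):
- Acceptance blind to arm, no effect: both the all-randomised and the acceptor analysis are centred on zero, with type I error 5.1%.
- Acceptance blind to arm, true effect 1.8: all-randomised gives 1.53, acceptors 1.80, two-stage least squares 1.79.
- Acceptance made to depend on arm, no effect: acceptors are biased by −0.21 with type I error 6.9%; all-randomised stays at 4.8%.

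A separate simulation at 15% declining put the precision gain over two-stage least squares at 8 to 10%. The formulas hold the residual SD fixed. Mixing treated and untreated people in one arm widens it, so the true gain may be somewhat larger, by an amount that depends on assumptions the protocol does not give.

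**The case against.** A reader might infer that the H1 primary set should itself be reduced to acceptors. The documents do not support that. The Background names dilution as a known cost of the design, Sample size calculations pays for it, and the resulting 90% exceeds the 80% design target. The all-randomised test also stays valid if blinding at the call failed, which the acceptor comparison does not. It keeps one population across the laser arm's comparisons, and changing a stated primary set after recruitment has closed would invite criticism. All of this stands.

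A reader might also infer that the diluted estimate would be held against 1.8 and 6 and fall short. Those values appear only in the sample size calculation. The Statistical analyses section tests at the 5% level and sets no such threshold for the estimate.

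A larger gain can be had by assuming 30% declining, where pain power would be 75.3% against 88.5% and the acceptor interval 16% narrower. Nothing in the protocol supports that rate. It calls 15% conservative, and the review it cites reports an interquartile range for crossover of 2.6% to 15%.

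Finally, the planned secondary analysis targets full adherence. The protocol sets a minimum of eight sessions and records attendance, so adherence may mean more than acceptance. Acceptors analysed regardless of attendance do not estimate that, and two-stage least squares should remain for it. Balanced decline rates alone would not show that the same kinds of people declined in each arm. Both points limit the recommendation without removing it.

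**Conclusion.** The point holds as a modest improvement to one secondary analysis. For laser versus sham only, and where adherence means taking up the offer, two-stage least squares gives an interval about 8% wider than a direct comparison of acceptors at the protocol's 15% non-consent, and about 5% wider at 8.9%. Both estimate the same effect in those who took up treatment. The primary all-randomised analysis is sound and should not change.

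The result rests on blinding at the consent call having held, as the Procedure section states, and on equal expected acceptance in the two laser arms. It also takes loss to follow-up to be unrelated to acceptance and the residual SD to be the same with and without decliners. It does not extend to H2, H3, H4 or any other contrast with needle or no treatment.

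**What to change.** Before unblinding, add to the secondary analyses: for laser versus sham, the effect in those who took up treatment is estimated by comparing all participants who accepted the laser offer, in the group to which they were randomised, regardless of sessions attended or later withdrawal. Only those who declined at the blinded call are left out.

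Report this beside the all-randomised primary result. Give decline rates and the baseline characteristics of decliners for each laser arm, as a check on the blinding on which the estimate depends. Retain two-stage least squares for contrasts with needle or no treatment, and for any definition of full adherence based on sessions.

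No new data are needed. The cost is one additional analysis set for one contrast, and reliance on the blinding of the consent call, which the descriptive check can support but not prove.
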